### Healthy controls

Healthy controls that satisfy the requirements: (1) have no history of stroke or impaired motor function; (2) are right-handed between the ages of 30 and 80; (3) have no metallic objects in their bodies and no fMRI or TMS contraindications; (4) have not undergone disease-related acupuncture or exercise therapy in the previous month; (5) understand and agree with relevant research content and volunteer to sign the informed consent form can be included in this study.

While those (1) with significant conditions, such as uncontrollable hypertension, arrhythmia, major coronary heart disease, or diabetes complications are not well-controlled, or have epilepsy, serious organ failure, and second attack of stroke, etc.; (2) with unstable vital signs; (3) are susceptible to co-infection, hemorrhage, tumor, pregnant women, postoperative dysfunction patients; (4) get other Traditional Chinese Medicine rehabilitation intervention other than acupuncture during the waiting period; (5) with linguistic or cognitive impairment; (6) with a history of mental illness or long-term sedative use; (7) with conditions that prevent exercise will be excluded.

### Interventions

PSD participants will be randomized to the ocular acupuncture (OA) group, the kinesitherapy (KT) group, or the OAKT group after enrollment.

Subjects in the OAKT group will undergo kinesitherapy after receiving ocular acupuncture stimulation at the “Upper-Jiao Area” (ACU 1), “Lower-Jiao Area” (ACU 2), “Liver Area” (ACU 3), and “Kidney Area” (ACU 4) (16) (Figure 2). This involves a series of advised exercise training consisting of warm-up exercises (low levels of aerobic exercise), exercise training (including aerobic training, walking training, treadmill training, resistance training, upper limb flexion adduction-abduction exercise, lower extremity knee flexion-extension exercise, flexibility training), and relaxation training (stretching exercise) (46). Needles for ocular acupuncture will remain embedded until the day's exercise training is finished. OAKT will be manipulated once a day, 5 days a week, for 4 weeks, with 2 days off between courses. Sweating, breathing, pulse, and blood pressure measures will be used to adjust the exercise prescription.

**Figure 2 F2:**
[figure not shown]
Location of ocular acupoints.

Subjects in the OA group will receive ocular acupuncture stimulation at the same acupoints of that in the OAKT group, without any exercise training of any kind.

Subjects in the KT group will undertake the same kinesitherapy as well as that in the OAKT group, without ocular acupuncture stimulation.

Healthy subjects will only get clinical, functional imaging, and electrophysiological evaluation without any therapy after enrollment and on the last day of the fourth week.

### Outcomes

#### Clinical outcomes

MMT Freehand Muscle Strength Grading and Simplify Fugl-Meyer grading will be evaluated at baseline and study completion. With 11 grades, MMT is used for measuring muscle contraction force based on muscle ability to accomplish gravity-support, anti-gravity, or anti-resistance tasks. Muscle strength increases with grade level. Fugl-Meyer is a motor function evaluation scale that consists of 33 upper-limb and 17 lower-limb subscales. Each subscale is worth 0 to 2 points, for a total score of 100. The motor function improves with a higher score.

#### Functional neuroimaging outcomes

A 3.0 Tesla high-field full-body magnetic resonance imaging system will be used for functional neuroimaging. Bold-fMRI data is acquired in the resting state following structural image scanning with a three-dimensional fast-spoiled gradient-recalled sequence and functional image scanning with a Gradient-Echo-Planar Imaging for 10 min, covering the entire brain, cerebellum, and brain stem. The parameters for scanning structural images include layer a thickness of 1 mm, a Repetition Time/Echo Time (TR/TE) of 2,700 ms/3.39 ms, Field of Vision (FOV) of 256 mm^2^, Matrix of 256 × 256, a Flip Angle of 7°, and an in-plane resolution of 1 × 1 mm. The settings for functional image scanning include a slice thickness of 5 mm, a TR/TE of 2,000 ms/30 ms, Matrix of 64 x 64, FOV of 240 mm^2^, and a Flip Angle of 90°.

The original fMRI data in DICOM format will be copied to a computer and converted by MRIcro software into an analyzable.img file format. The software packages Data Processing Assistant for Resting-State fMRI (DPARSF) and the statistical parametric mapping software package (SPM12) in Matlab (Mathworks, Inc., Natick, Massachusetts) will be utilized to preprocess the fMRI data. Preprocessing steps include (1) realign, all images of each selected subject whose translation in all directions (x, y, z) is <1 mm and rotation angle is <1 degree will be aligned with its first image for further analysis; (2) Spatial normalization, registers images of all subjects to the standard template of Montreal Neurological Institute (MNI) neurological spatial coordinates and re-cuts the voxel to 3 mm 3 for data standardization and individual comparability; (3) slice-timing correction, uses a mathematical approach to collect all images at the same time point by default, with the intermediate time point as the reference layer; (4) smoothing with an 8 mm full width at half maximum (FWHM) kernel to reduce spatial noise, as well as errors caused by spatial normalization; (5) Detrending with linear regression and filtering with a frequency window of 0.01–0.08 Hz to remove low frequency noise caused by respiration, heartbeat, and other physiological factors, as well as high frequency noise from the MRI scanner itself.

Regional homogeneity (ReHo), a typical fMRI analysis, can indirectly reflect the time synchronization of spontaneous neural function activities in a specific brain region. The Kendall's Coefficient Concordance (KCC) will be used to quantify the local consistency of time series between each voxel in the entire brain and the nearest 26 voxels around it by using REST software in Matlab. Each individual receives a ReHo image by computing the KCC value of each voxel. After normalization, the average ReHo image of each subject will be derived by dividing the KCC value of each voxel by the average KCC value of the entire brain. The estimated ReHo value corresponds to the KCC value, which runs from 0 to 1. The closer it is to 1, the more consistent this voxel's activity is in time series with its neighboring voxels, reflecting brain local neuronal activity synchronization. The calculation is expressed as follows:

$$\begin{array}{l} \text{ReHo}=\frac{\sum {\left({\text{R}}_{\text{i}}\right)}^{2}-\text{n}{\left(\text{R}\right)}^{2}}{{\text{k}}^{2}\left({\text{n}}^{3}-\text{n}\right)/12} \end{array}$$

The SPM12 in Matlab will be used to analyze the obtained ReHo value. MNI coordinates of the associated regions, the size of the clusters, and the active or positive brain regions will all be noted before and after the intervention.

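### Smoothing the images with an 8 mm kernel before computing ReHo inflates and compresses ReHo; slice-timing after normalisation is a lesser fault in the same list

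*Protocol article*

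**What the plan says.** Protocol article, Functional neuroimaging outcomes, gives preprocessing as a numbered list that opens "Preprocessing steps include (1) realign, all images of each selected subject". The order is:

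1. realignment;
2. normalisation to MNI space, which "re-cuts the voxel to 3 mm 3 for data standardization and individual comparability";
3. slice-timing correction, which "uses a mathematical approach to collect all images at the same time point by default";
4. "smoothing with an 8 mm full width at half maximum (FWHM) kernel";
5. detrending and band-pass filtering at 0.01–0.08 Hz.

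The ReHo text follows. KCC is used to "quantify the local consistency of time series between each voxel in the entire brain and the nearest 26 voxels around it", on a scale from 0 to 1, and each map is divided by its whole-brain mean. A value near 1 is interpreted as strong local neuronal synchrony. Neuroimaging data analysis then applies paired t-tests in SPM12. Smoothing appears once in the article, before ReHo. Nothing says that ReHo uses unsmoothed images or that the ReHo maps are smoothed afterwards.

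**The concern.** ReHo asks how alike the time series of adjacent voxels are. A smoothing kernel makes adjacent series alike by construction, because each becomes a weighted average of largely the same voxels. When the kernel is about as wide as the neighbourhood, a large part of the KCC level comes from the processing. KCC cannot exceed 1, so a raised floor leaves less room for real differences. The kernel also brings in signal from outside the 27 voxels, so the value no longer describes only that neighbourhood.

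Every fMRI result named in Study setting (ReHo value, cluster size, regions, MNI coordinates) comes from these maps, and so do the correlations with MMT and Fugl-Meyer. With 15 patients per arm there is little sensitivity to spare.

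Slice-timing is a separate matter. After reslicing to the 3 mm MNI grid, a slice is no longer one of the acquired 5 mm slices, so acquisition times cannot be assigned to it correctly.

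**Working it through.** The article states no figure to reproduce. The check uses its processing settings.

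**Inputs (Functional neuroimaging outcomes).** Functional acquisition: "a slice thickness of 5 mm, a TR/TE of 2,000 ms/30 ms, Matrix of 64 x 64, FOV of 240 mm^2". Reading the field of view as 240 mm per side, in-plane voxels are 240/64 = 3.75 mm. Taking the 10-minute scan as the functional run, there are 600/2 = 300 volumes. Voxels are 3 mm after normalisation, the kernel is 8 mm FWHM, and the neighbourhood is 27 voxels, 3 × 3 = 9 mm wide.

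**Correlation created by the kernel.** Kernel SD = 8/2.3548 = 3.40 mm. For independent noise, the correlation at distance d after smoothing is exp(−d²/(4·SD²)):
- face neighbours, 3 mm: 0.82;
- edge neighbours, 4.24 mm: 0.68;
- centre to cube corner, 5.20 mm: 0.56.

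The mean over all pairs in the cube is 0.495, so KCC ≈ (1 + 26 × 0.495)/27 = 0.51. Without smoothing, theory gives 1/27 = 0.037.

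**Simulated pure noise** (300 volumes, TR 2 s, 0.01–0.08 Hz filter, the article's KCC formula):

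| Starting data | Unsmoothed | 8 mm first | Ratio |
|---|---|---|---|
| Independent 3 mm voxels | 0.037 | 0.50 | about 13 |
| 3.75 × 3.75 × 5 mm voxels resampled linearly to 3 mm | 0.18 | 0.57 | about 3 |

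The second row is closer to the stated acquisition, since resampling alone already correlates neighbours.

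**Simulated true signal.** Here a shared signal makes up 10% or 30% of voxel variance, starting from independent 3 mm voxels, with 25 runs per cell. Signal shares and region sizes are assumptions.

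| Active region | Processing | KCC at 10% | KCC at 30% | Difference | Ratio |
|---|---|---|---|---|---|
| 27 voxels | unsmoothed | 0.130 | 0.318 | 0.188 | 2.4 |
| 27 voxels | 8 mm first | 0.709 | 0.854 | 0.145 | 1.2 |
| 343 voxels | unsmoothed | 0.136 | 0.311 | 0.175 | 2.3 |
| 343 voxels | 8 mm first | 0.929 | 0.980 | 0.051 | 1.05 |

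- Compression: the difference shrinks in both regions, most in the large one.
- Dependence on outside signal: at a 10% share, both regions score about 0.13 unsmoothed, but 0.71 and 0.93 after smoothing.
- Reversed ranking: smoothed, the small region at 30% (0.85) falls below the large region at 10% (0.93). Unsmoothed they rank correctly (0.32 against 0.14).
- Scaling: dividing a map by one number leaves the ratio of any two voxels in it unchanged, so it cannot restore the lost ratios or the ranking.

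**Loss against simulation noise.** Divide each difference by the root mean square of the two run-to-run SDs.
- Small region: 0.188/0.0235 = 8.0 unsmoothed (SDs 0.018, 0.028); 0.145/0.0235 = 6.2 smoothed (SDs 0.028, 0.018). About 77% is kept.
- Large region: 0.175/0.0259 = 6.7 unsmoothed (SDs 0.016, 0.033); 0.051/0.0089 = 5.7 smoothed (SDs 0.012, 0.004). About 84% is kept.

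These SDs contain no between-patient variation.

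**Slice-timing.** With a mid-volume reference and TR 2 s, shifts are at most about 1 s. The shortest period kept by the filter is 1/0.08 = 12.5 s, so the shift is at most 1/12.5 = 8% of a cycle. The article gives no slice order or slice count, so the actual error cannot be derived.

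**The case against.** A reader might infer that ReHo would measure the kernel and nothing else. The article's settings do not support that: in the simulations, smoothed KCC still rises with true synchrony in both regions. Nor does the order by itself manufacture differences between visits or groups. The kernel is common to all scans, the tests are paired, and division by the whole-brain mean removes part of the shared offset. Both points stand and limit the claim.

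The 13-fold rise assumes voxels that are independent at 3 mm. Given the stated acquisition, the roughly 3-fold rise (0.18 to 0.57) is the fairer figure.

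The loss in detecting a difference is moderate. A rough comparison (12 runs per cell, assumed signals) of smoothing first against smoothing the ReHo map afterwards kept roughly 60–85% of the standardised difference, for example 2.5 against 3.0 and 4.2 against 7.1.

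Contamination across lesion borders is tempting as a further argument, but smoothing the ReHo map also mixes tissue across borders, so it is not specific to this order.

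Finally, the list is introduced as what preprocessing includes, in a condensed article, so the order actually run may differ. That is possible. But the steps are numbered and no other order is given, so anyone following the text would smooth first. If practice differs, the text needs correcting.

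**Conclusion.** The point holds as distortion and lost sensitivity in the only fMRI measure. As written, the pipeline raises the pure-noise level of KCC to 0.50–0.57 on a 0–1 scale (from 0.04, or 0.18 with resampling), compresses true differences towards the ceiling, and makes ReHo depend on the extent of the surrounding signal. Whole-brain scaling does not repair this. The noise figures rest on spatially independent noise in the acquired or 3 mm voxels and on 300 volumes. The contrast figures rest on assumed signal shares and region sizes, so they show direction and rough size only.

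Slice-timing after normalisation is also wrongly placed, but it is secondary, does not cause the kernel effect, and probably matters little at this TR and filter band.

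This should be fixed before analysis. It does not touch the MMT, Fugl-Meyer or TMS-MEP outcomes themselves, and it can be corrected from the raw images.

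**What to change.** Restate the order as:

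1. slice-timing correction;
2. realignment;
3. normalisation to 3 mm;
4. detrending and 0.01–0.08 Hz filtering;
5. ReHo on these unsmoothed images;
6. division by the whole-brain mean;
7. smoothing of the ReHo maps;
8. the SPM12 tests.

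If this is already the order in use, correct the text to say so. Either way, fix it in writing before analysis so that the pipeline is not chosen after seeing results. The cost is rewording and reprocessing in the software already named. No new scans are needed, because the plan copies and stores the original DICOM data.

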## Methods

### Study setting

This is a prospective functional neuroimaging and neurotic electrophysiological study with a case-control design between the PSD with the HC groups and a randomized controlled design within the 3 PSD groups (OAKT group, ocular acupuncture group, and kinesitherapy group). Using fMRI scanning and the TMS-MEP technique, we will assess the central-peripheral neuronal function changes of PSD as well as the coupling effects of OAKT on them. This trial was authorized by the Institutional Review Board of Chengdu University of Traditional Chinese Medicine in April 2022 (reference number: 2022KL-027) and registered (ChiCTR2200060483) at the Chinese Clinical Trial Registry in June 2022. We plan to enroll 90 participants at the Hospital of Chengdu University of Traditional Chinese Medicine from Aug 31, 2022, to Dec 31, 2023. All eligible subjects will be evaluated by fMRI scanning, TMS-MEP examination, and the MMT and Fugl-Mayer assessment following enrollment and on the last day after 4-weeks of waiting (for HC subjects) or intervention (ocular acupuncture, kinesitherapy, or OAKT for PSD subjects, respectively). MMT and Fugl-Meyer score, ReHo value, cluster size, active or positive brain regions and their MNI coordinates, amplitude (AMP), potential latency (PL), and central motor conduction time (CMCT) in the cortical region will be measured, and Pearson correlation analysis will be performed to assess the relationship between clinical and imaging outcomes. This trial will be conducted in accordance with the Standard Protocol Items: Recommendations for Interventional Trials (SPIRIT) (43). Figure 1 displays a flow diagram.

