#### Neuroimaging data analysis

SPM12 software will be used to perform paired *t*-tests on the acquired ReHo value. The statistical threshold voxel-level will be *P* < 0.001 with multiple comparisons corrected by FEW (family-wise error), cluster level α < 0.05. More than 10 continuous voxels will be significant.

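### Cluster size, positive regions and coordinates are listed as before/after imaging outcomes, but they are features of a thresholded group map, and comparing such lists does not measure change

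*Protocol article*

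**What the plan says.** Study setting in the protocol article gives one list of what will be measured at enrolment and after four weeks. It includes "MMT and Fugl-Meyer score, ReHo value, cluster size, active or positive brain regions and their MNI coordinates", followed by the TMS-MEP amplitude, latency and conduction time. Functional neuroimaging outcomes describes how each person gets a ReHo image, then adds that coordinates, "the size of the clusters, and the active or positive brain regions will all be noted before and after the intervention".

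Neuroimaging data analysis names one test: "SPM12 software will be used to perform paired *t*-tests on the acquired ReHo value". Its thresholds are: "The statistical threshold voxel-level will be *P* < 0.001" with family-wise error correction, "cluster level α < 0.05", and "More than 10 continuous voxels will be significant". No test is given for cluster size or for lists of regions. Statistical methods restricts the analysis to people with complete data at both assessments. Sample size sets 15 patients in each of the three arms and 45 controls.

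**The concern.** The outcome list mixes two kinds of quantity. MMT, Fugl-Meyer, ReHo and the electrophysiological indices have a value for each patient at each visit, so a change and its standard error can be formed. Cluster size, positive status and peak coordinates exist only once a group map has been computed and cut at a threshold. They reflect effect, noise, threshold and sample size together, and they carry no standard error. A region can be above threshold at one visit and below it at the other without having changed significantly.

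Recording these features before and after treatment, as outcomes, invites a reader to take a larger or newly positive cluster as an effect of treatment. The stated test cannot supply such lists. The trial's own question, whether OAKT changes brain function differently from its components, needs a contrast of patient-level change.

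**Working it through.** **Setting the sections side by side.** A paired t-test takes each patient's after-minus-before ReHo at each voxel and returns one map of change, with one set of clusters and coordinates. It yields neither a before list nor an after list. Visit-specific lists need a separate contrast at each visit, and Neuroimaging data analysis names none.

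**Inputs from the protocol article.** 15 per arm and 45 controls (3 × 15 + 45 = 90, which reproduces the stated total); voxel P < 0.001, sidedness not stated; more than 10 voxels; 3 mm voxels; 8 mm smoothing.

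**Assumed inputs.** The article gives no effect size, standard deviation or drop-out rate. All standardised effects d below are assumptions, as is n = 12 for an arm after losses.

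**Check 1: before versus after within an arm, with no true change.** Let p be the probability that a location with true standardised effect d passes two-sided P < 0.001 at n = 15 (noncentral t, 14 degrees of freedom, noncentrality d√15). With independent noise at the two visits, the chance of being positive at exactly one visit is 2p(1 − p).

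| d | p | 2p(1 − p) |
|---|---|---|
| 0.6 | 0.083 | 0.15 |
| 0.8 | 0.223 | 0.35 |
| 1.0 | 0.442 | 0.49 |
| 1.2 | 0.679 | 0.44 |

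A simulation of smoothed maps (one fixed effect with peak d = 1, one-sided voxel threshold, 120 runs) gave before and after cluster sizes that differed by a median of 45% of the larger, and by more than half in 41% of runs, with no change in truth. Noise was again independent between visits. Scans of the same patients are correlated, which would reduce these figures without removing the problem.

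**Check 2: dependence on the threshold.** For d = 0.8 and n = 15, the chance of passing is 56%, 22% and 6% at two-sided P < 0.01, 0.001 and 0.0001. Simulated median cluster sizes at one-sided cut-offs of the same values were about 386, 87 and 19 voxels.

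**Check 3: dependence on n.** This bears only on comparisons between arms or with the controls, because the complete-data rule gives the same n at both visits within an arm. The smallest observed standardised effect that passes one-sided P < 0.001 is t(0.999, n − 1)/√n, which is 0.978 at n = 15 and 1.162 at n = 12. For an effect with a Gaussian profile, the volume above threshold is proportional to [ln(peak/threshold)]^1.5. The n = 12 to n = 15 ratio is then:

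- peak 1.3: (0.112/0.285)^1.5 = 0.25
- peak 1.5: (0.255/0.428)^1.5 = 0.46
- peak 2.0: (0.543/0.715)^1.5 = 0.66

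For d = 0.8, the chance of passing two-sided P < 0.001 is 13%, 22% and 96% at n = 12, 15 and 45. A map of 45 controls would therefore show many more positive regions than a 15-patient arm with the same underlying effect.

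**The case against.** The strongest reply is that the article only notes these descriptors. It tests none of them and nowhere says that a larger cluster means benefit. Change is tested on ReHo, and reporting where a significant paired difference lies, and how far it extends, is ordinary practice. This stands. A reader might infer that the plan will judge OAKT by comparing cluster sizes, or that cluster information has no place in the report. The documents support neither reading.

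A second reply is that sample size cannot distort the before/after comparison, since only people with both assessments are analysed. This also stands, and it confines the n = 12 and n = 45 figures to comparisons across groups, which the article does not propose.

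A third reply is that the case-control design allows a patient-versus-control contrast at each visit, which would give proper before and after lists. That is possible, but the imaging analysis section does not state it. Even then, a region significant at one visit and not at the other would not be a test of change.

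What remains is that the descriptors are listed as measured outcomes at two time points, alongside patient-level variables, and that the stated test does not generate them in that form.

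**Conclusion.** The point holds as a fault in the definition of the imaging outcomes. Before/after lists of clusters and positive regions are not a valid measure of change, and Study setting and Functional neuroimaging outcomes do not agree with the paired test in Neuroimaging data analysis. No stated error rate or sample size is wrong on this account.

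The size of the problem can only be illustrated. With 15 patients and no true change, a location appears at just one visit 15% to 49% of the time for assumed d of 0.6 to 1.2, and less often once correlation between visits is allowed for. Cluster-size ratios across different n rest on assumed peaks and assumed losses. It would be wrong to conclude that unequal drop-out explains before/after differences within an arm, or that clusters of the paired difference map are unusable.

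**What to change.** In Study setting and Functional neuroimaging outcomes, make each patient's ReHo value at each visit the imaging outcome. It can be voxelwise, or the mean in prespecified regions such as the primary motor cortex and thalamus, which the Discussion names as targets. In Neuroimaging data analysis, keep the within-group paired test and add an analysis of pre-post ReHo change between the three randomised arms. Report cluster size and coordinates only to describe where a tested contrast is significant, and state that they will not be compared between visits or arms.

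The cost is a change of wording, a small amount of extra analysis, and the loss of the before/after lists as outcomes. No new data are needed, because each participant already gets a ReHo image.
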